### Time plan

The inclusion of participants started in November 2022. Interviews and focus groups will be conducted between January 2023 and December 2024. Inclusion as well as data collection is estimated to be completed in December 2024.

### Allocation and blinding

Eligible participants will be randomized to either the intervention (TM) or control (UCM) group. The randomization schedule will be developed by a member of the research team not involved in participant recruitment or contact with referring agencies. The randomization sequence will be developed a priori by site (*n* = 3) using the online randomizer random.org with 50% allocation between arms. Results of the randomization for individual participants will be communicated following inclusion and collection of baseline measurement data.

Participants, service providers, and research staff will not be blinded to final participant allocation. Data collection subsequent to baseline measurements will not be blinded.

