**Fig. 1 Fig1:**
[figure not shown]
Overview over the design of the study

This study will take place within the local eldercare authorities of three municipalities in southwestern Sweden. The largest municipality has just over 100,000 inhabitants and about 22,000 inhabitants aged 65 + . The two smaller municipalities have just under 47 000 inhabitants combined. Approximately 11,000 of whom are aged 65 + . The study will be performed in collaboration between researchers from the Department of Social Work at the University of Gothenburg, the Department of Work Life and Social Welfare at the University of Borås, the School of Health and Welfare at Jönköping University, and managers, research assistants and staff from three municipal eldercare authorities. Continuous meetings and workshops with collaborators will be held throughout the study period, to monitor participant enrolment and adherence to study protocols.

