### Recruitment and eligibility criteria

The target group for this study is older people with mild to moderate dementia who use home care services provided by municipal eldercare authorities. Service users will be identified by care managers, healthcare staff or a specialized dementia team. At first contact, potential participants will receive brief information about the study and be offered the opportunity to participate in screening tests for mild to moderate dementia. It will be made clear that the choice to participate in the study (or not) will not affect receipt of eldercare. On expression of interest to participate in the study, permission will be sought by home care service providers to forward contact details to the research team. A research assistant will contact individuals referred to the study to arrange a convenient time to meet. At this visit, written and verbal informed consent will be obtained, and baseline data will be collected.

Eligibility criteria:Participants are aged 65 or older.Participants receive home care services from the eldercare authority in one of the three participating municipalities.Participants are assessed as having mild to moderate dementia which is defined as scoring between 12–23 on the mini-mental state examination (MMSE).

According to preliminary power calculations, we plan to include 50 participants in each study arm. The calculation was made based on what is needed to detect a moderate difference (0.25 effect size) with 0.9 power, p = 0.05 [25]. Significant differences over time in involvement were found using the Involvement Measure Scale (IMS) in a sample of 18 in a previous study [11].

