### Analysis

Study data will be pooled with pilot data for analysis. To answer RQ1 and RQ2, we will perform descriptive and comparative statistical analyses as well as qualitative thematic analysis [37]. Statistical data analysis methods will be chosen based on data characteristics (e.g., ANOVA, Kruskal–Wallis). Baseline differences between groups will be controlled for in the final analyses. Sensitivity analyses will be conducted (e.g., TOT vs ITT analysis). Methods for handling missing data will be determined based on a missing data analysis to determine the nature of the missingness (e.g., MCAR). Fidelity and implementation will be tested for their impact on results. To check for comparison group equivalence, we will compare the pre-test dementia scores, functional ability and demographic variables of the two groups. When evaluating the video-recordings of the conversations, using the “OPTION scale”, inter-rater reliability will be tested. To interpret the effects of the intervention, qualitative thematic analyses [37] of the participants’ and staff’s experiences as expressed in focus group and individual interview data will be conducted.

For RQ3 we will perform descriptive analyses of survey-data as well as qualitative thematic analysis of focus group and individual interview data. This will provide analysis of patterns and themes in the interview and focus group statements. The qualitative data will enable an analysis of similarities as well as differences in the experiences of the persons involved in the study, on an individual as well as a group level. In addition, a mixed method approach [38] will be used linking descriptive statistics and qualitative analysis.

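### Randomisation is generated separately by municipality, but the Analysis section makes no provision for site and picks covariates by observed imbalance

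*Protocol article*

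**What the plan says.** All references are to the protocol article.

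- Design and setting: "This study will take place within the local eldercare authorities of three municipalities in southwestern Sweden".
- Allocation and blinding: "The randomization sequence will be developed a priori by site", for three sites, "using the online randomizer random.org with 50% allocation between arms". No blocks or other restriction that would force balance within a site are described.
- Analysis, on method: "Statistical data analysis methods will be chosen based on data characteristics (e.g., ANOVA, Kruskal–Wallis"). Both methods are examples, and no model is fixed.
- Analysis, on covariates: "Baseline differences between groups will be controlled for in the final analyses".
- Analysis, on the baseline comparison: "we will compare the pre-test dementia scores, functional ability and demographic variables of the two groups". Site is not among the variables listed.
- Recruitment and eligibility criteria: "we plan to include 50 participants in each study arm". The calculation is described without reference to site.

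**The concern.** Generating the sequence by site makes municipality a stratification factor. The natural analysis then compares arms within municipality. The only stated route into the model is an observed difference between arms at baseline, and that is the wrong criterion for a stratification factor. The better the site-wise allocation balances the arms, the less likely site is to show a difference and be adjusted for. Its value in the model comes from its relation to the outcome, whatever the imbalance. Of the two example methods, ANOVA can carry a site factor, but a plain Kruskal–Wallis test cannot.

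Site could matter here. OPTION rates service providers' behaviour, and the providers work for three separate authorities. The Interventions section says that the TM material was adapted with providers in one of the participating municipalities, so familiarity with TM may differ between sites.

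At stake is some precision, and under blocked lists a test that rejects too rarely. Nothing here points to an inflated false-positive rate. Because allocation is not blinded, it also helps to settle the covariates before outcomes are compared.

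**Working it through.** **Inputs from the article.** 50 per arm; three sites; 1:1 allocation; effect size 0.25, metric not stated; power 0.9; p = 0.05, taken here as two-sided.

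**Assumptions.** (a) The share of outcome variance explained by site, R², from 0 to 0.20; the article gives no figure. (b) A standardised difference d = 0.5, which is how 0.25 reads if it is Cohen's f (d = 2f for two equal groups) and fits the label *moderate*. (c) For the simulation, site shares of 68, 16 and 16 out of 100, suggested by about 22,000 inhabitants aged 65 or over in the largest municipality and about 11,000 in the other two together.

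**Step 1: the article's own sample size.** The plan is to "detect a moderate difference (0.25 effect size) with 0.9 power, p = 0.05". For two means, n per arm = 2(1.960 + 1.282)²/d².
- d = 0.5: 2 × 10.51/0.25 = 84.1, so 85 per arm. Power at 50 per arm is Φ(0.5/0.2 − 1.96) = Φ(0.54) = 70.5%.
- d = 0.25: 2 × 10.51/0.0625 = 336.2, so 337 per arm. Power at 50 per arm is 24%.

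Neither reading gives 50. A between-group test on two repeated measurements gives a total of 96 to 104 if the T1–T2 correlation is about 0.1 to 0.2, which is not stated. That is a separate matter; here, 70.5% serves only as the baseline for d = 0.5.

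**Step 2: lists blocked within site.** Set the outcome variance within an arm to 1. With forced balance, site differences cancel from the comparison of arms:
- true SE = √((1 − R²) × 2/50)
- SE reported without site = √(2/50) = 0.200
- power with site = Φ(0.5/true SE − 1.96)
- power without site = Φ((0.5 − 1.96 × 0.200)/true SE)
- type I error without site = 2[1 − Φ(1.96 × 0.200/true SE)]

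For R² = 0.10, the true SE is √0.9 × 0.2 = 0.1897. Power with site is Φ(0.675) = 75.0%; without site it is Φ(0.569) = 71.5%. Type I error without site is 2[1 − Φ(2.066)] = 0.039.

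| Site R² (assumed) | Type I error without site | Power without site | Power with site | Gain, points |
|---|---|---|---|---|
| 0 | 0.050 | 70.5% | 70.5% | 0 |
| 0.02 | 0.048 | 70.7% | 71.4% | 0.7 |
| 0.05 | 0.044 | 71.0% | 72.7% | 1.7 |
| 0.10 | 0.039 | 71.5% | 75.0% | 3.5 |
| 0.20 | 0.028 | 72.7% | 79.8% | 7.1 |

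A simulation with 8,000 replicates per setting agrees. At R² = 0.10, type I error without site was 0.040 and power 70.1% without against 74.0% with site; at 0.20, 0.031 and 71.8% against 78.6%. If 0.25 is read as d, the gains are similar: at R² = 0.10, power is 22.7% without site and 26.0% with it, a gain of 3.3 points.

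**Step 3: lists not blocked.** In the same simulation with simple randomisation within site, the test without site kept its level: 0.046 to 0.053 across R² from 0 to 0.20, against a Monte Carlo standard error of √(0.05 × 0.95/8000) = 0.0024. Power at d = 0.5, without and with site:

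| Site R² (assumed) | Without site | With site | Difference, points |
|---|---|---|---|
| 0 | 67.4% | 66.7% | −0.7 |
| 0.02 | 69.0% | 69.1% | 0.1 |
| 0.05 | 69.8% | 71.2% | 1.4 |
| 0.10 | 69.3% | 72.6% | 3.3 |
| 0.20 | 68.6% | 77.6% | 9.0 |

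**Step 4: cost of including site when it is irrelevant.** Residual degrees of freedom fall from 100 − 2 = 98 to 100 − 4 = 96. At R² = 0, simulated power was 69.7% without and 69.6% with site under blocking, and 67.4% against 66.7% without blocking. The loss is below one point in both.

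**The case against.** A reader might infer that the plan excludes site from the analysis, that its standard errors will therefore be wrong, and that power will certainly be lost. The article does not support any of these.

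- **Exclusion.** The Analysis section leaves the model open. ANOVA can include site, no covariate list is closed, and an analysis plan that is not shown may name municipality. This stands: the text makes no provision for site, which is less than leaving it out. But the article does state a rule for choosing covariates, and that rule suits a stratification factor badly. The point rests on the stated rule and not on silence alone.
- **Wrong standard errors.** This needs forced balance within site. The article gives separate lists and a 50% allocation but no blocking. With unblocked lists the test without site is valid, and site could by chance be unbalanced and so be noticed. This also stands.
- **Certain loss of power.** The article gives no site variance. All service providers had the same two-day TM training and the same binders, and control needs assessments use the common IBIC tool, which argues for modest site differences. At R² of 0.05 or below, the gain from adjustment is under 2 points.

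The error is also in the safe direction, and the shortfall in Step 1 is far larger than anything site adjustment can recover. Neither is a reason to leave the covariate rule as it is, since the remedy costs almost nothing.

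**Conclusion.** The point holds as a mismatch between how participants are allocated and how covariates are chosen. Following the Analysis section as written would not reliably bring municipality into the comparison, and a plain Kruskal–Wallis test could not include it.

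The consequence is conditional. With blocked lists and a prognostic site, the test without site is conservative; with unblocked lists it is valid but less efficient. The benefit of adjustment ranges from nil to about 7 points of power under forced balance as site R² goes from 0 to 0.20, and to about 9 points in the simulation without blocking. These figures rest on an assumed d = 0.5 and assumed values of R². The upper end should not be taken as expected. This is an inexpensive improvement to the plan and not a threat to the trial's validity.

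**What to change.** Add to the Analysis section: *All between-arm comparisons of IMS and OPTION include municipality (three levels) as a fixed factor, whether or not the arms differ on it at baseline, because randomisation is by site. If a rank test is chosen, the site-stratified (van Elteren) version is used.* State under Allocation and blinding whether the site lists were blocked, so that a reader can tell which of the two situations applies.

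The cost is two degrees of freedom and no new data. The sentence is right for blocked and unblocked lists alike, and should be fixed before outcomes are compared by arm.

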### Participant timeline

Study participants will be offered the screening test within two weeks from their first contact with research staff (Fig. 2). Following screening, study participants will be randomized to TM or UCM. Two weeks following screening, participants will have a needs assessment conversation with a care manager. Approximately three weeks post conversation with care managers, a meeting with home care service staff will take place. Directly following participants' conversation with care managers and home care staff, a researcher will conduct a standardized interview using the IMS. In 2023 or 2024, participants as well as their relatives will be invited to take part in qualitative interviews with one of the researchers.

**Fig. 2 Fig2:**
[figure not shown]
Schedule of enrolment, interventions, and assessments

### Interventions

#### TalkingMats (TM) intervention

Participants in the intervention group will use TM as a decision aid in needs assessment conversations as well as in conversations about the delivery of home care services. TM is a low-technology communication framework, designed to help people with communication difficulties express their views and was developed through research conducted at the University of Stirling in Scotland. TM uses a simple system of picture symbols which are placed on a textured mat. TM allows people to indicate their feelings about various options within a topic by placing the relevant image below a visual scale. Three sets of symbols are used. One set of symbols is used for the topics of the conversation, one set for the options within each topic, and one set consisting of a value scale under which the options are placed. Previous studies [11, 26] have found that the TM could be used by many people at all stages of dementia and that the use of TM improved participants’ ability to communicate compared with usual conversation methods. The use of TM allowed participants with dementia to communicate their needs and preferences with greater ease, helped them remain in control of their own daily living activities, and assisted them when facing difficult decisions.

In a previous pilot study conducted by our research team, all TM materials and procedures were adapted in collaboration with service providers in one of the municipalities participating in the present study. In addition, specific TM material was developed and adapted for the purpose of the present study. The specific topics and range of options within each topic for use within the TM framework have been identified in workshops with service providers using the World Health Organization’s International Classification of Functioning (ICF; [27]) and in line with the systematic needs-assessment tool “The Individual’s Needs in the Center” (IBIC) [28]. The material and procedures to be used in the present study have been tested, revised, and re-tested several times in preparation for this study. In September 2020, researchers and service providers tested the TM with older adults (acquaintances and/or service users). Subsequently, care managers, home care staff, and researchers tested and revised the TM material in reoccurring workshops held between autumn 2020 through 2021. All instructions and TM materials have been gathered in binders which have been provided to all care managers, home care staff, and research assistants involved in the study. All service providers and research assistants involved in the pilot study as well as the present study have received a two-day training in the use of TM from accredited TM trainers at the Dart Communication and Data Resource Centre, Region Västra Götaland, Sweden.

#### Control group

Participants in the control group will receive UCM for both the needs-assessment conversation and the conversations about home care service provision. The needs-assessment conversations are based on the systematic needs-assessment tool IBIC [28].

### Outcomes

#### Primary outcome measure—participants

##### Involvement Measure Scale (IMS)

The IMS measures older people’s involvement in conversations around care. IMS is made up of six questions from the Freedom of Choice Interview Schedule [29] which is a measure specifically designed for people with dementia and their family carers to indicate how they rate their involvement in a situation where they had to consider issues around care. Participants rate questions on a 4-point scale ranging from “never/none” to “always/all”. When evaluating the use of TM for people with dementia, Murphy et al. [11] used a slightly adapted IMS, that we have translated to Swedish for the purpose of the present study [30].

#### Primary outcome measure – service providers

##### OPTION scale

Service provider efforts to involve older people with mild to moderate dementia in conversations around needs-assessments and service delivery are measured with the OPTION- scale which has been found valid and reliable in previous research [31]. The scale is made up of 12 questions and has been translated for the present study. The 12-items are rated on a five-point scale ranging from participant “is not involved” to participant “is involved to a high degree”.

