### Aims and research questions

The aim of this study is to test and evaluate the use of TM as a decision aid in conversations regarding needs assessment and the delivery of home care services for older people with mild to moderate dementia within Swedish municipal eldercare. Specifically, this study will provide more insight into the extent to which TM impacts participants perception of their involvement in decision making and the extent to which TM promotes service providers’ efforts to involve service recipients in decision making. Moreover, the process by which TM is implemented into normal municipal eldercare will be studied closely. Using a mix of quantitative and a qualitative designs the following research questions will be answered:

RQ1. To what extent does TM impact participants’ perceived involvement in decision making in conversations regarding home care services compared with usual conversation methods (UCM)?RQ2. To what extent does TM impact service provider efforts to involve participants in decision making in conversations regarding home care services compared with UCM?RQ3. What are the barriers and facilitators of implementing TM as a decision aid in the context of Swedish municipal home care services for older people with mild to moderate dementia?

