#### Outcome data

Primary outcome data will be collected by the research team. Data on participant involvement in conversations around care, measured with the IMS, will be collected at two time points (T1, T2). T1 will be conducted directly after the needs assessment conversation and T2 will be conducted directly after the conversations about delivery of home care services. Data on service providers' efforts to involve participants in conversation will be obtained through video-recordings of the conversations. These recordings will be evaluated by the researchers using the OPTION scale.

The secondary outcome data will be collected through a survey to care managers and staff performing the intervention, consisting of the three implementation outcome measures AIM, IAM, and FIM. The survey will be administered at baseline (directly after the TM training), after 6 months, and after 12 months. Data on implementation fidelity will be obtained by evaluations of the video recorded clinical encounters, using the above-mentioned checklist.

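### OPTION is assigned to provider effort (RQ2), but its stated end-points grade the participant's involvement, so participant response could confound the RQ2 outcome

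*Protocol article*

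**What the plan says.** RQ2, under Aims and research questions, asks: "To what extent does TM impact service provider efforts to involve participants in decision making". RQ1 is kept separate and concerns the participants' own "perceived involvement in decision making in conversations regarding home care services compared with usual conversation methods (UCM").

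The Outcomes section gives each question its own primary outcome. For RQ1 it is the Involvement Measure Scale (IMS), which concerns the older person's "involvement in conversations around care. IMS is made up of six questions from the Freedom of Choice Interview Schedule" and is answered by the participants on a 4-point scale. For RQ2 it is OPTION, whose target is stated as "Service provider efforts to involve older people with mild to moderate dementia in conversations around needs-assessments and service delivery". On the content of OPTION the article says: "The scale is made up of 12 questions and has been translated for the present study". The response format follows: "The 12-items are rated on a five-point scale ranging from participant “is not involved” to participant “is involved to a high degree".

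Under Outcome data, the ratings are again described as data on providers' "efforts to involve participants in conversation will be obtained through video-recordings of the conversations", and "These recordings will be evaluated by the researchers using the OPTION scale". Under Allocation and blinding, research staff know the allocation and data collection after baseline is not blinded. The Analysis section plans an inter-rater reliability check for OPTION.

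**The concern.** The declared construct and the stated scoring rule have different subjects. The construct is something the provider does. The end-points describe a condition of the participant.

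The two can separate in this population, which is admitted across MMSE 12 to 23. A provider who explains, offers options and checks understanding may face a participant who stays passive; graded by the end-points, that conversation could score low. A provider who does little may face a participant who takes the lead, and that conversation could score high.

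The intervention also acts on what the camera sees of the participant. In TM the person places picture symbols under a visual scale, and a rater who is grading participant involvement may credit that activity in itself. What is at stake is the interpretation of RQ2: whether a difference between arms in OPTION shows that TM changes what providers do.

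**Working it through.** No figure in the protocol article bears on this point, so there is nothing to reproduce. The check sets the statements side by side.

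| Place in the protocol article | What is graded |
|---|---|
| Aims, RQ2 | Provider effort |
| Outcomes, OPTION, opening sentence | Provider effort |
| Data collection methods, Outcome data | Provider effort |
| Outcomes, OPTION, response scale | Participant's degree of involvement |

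Three statements of the construct point one way. The single stated scoring rule, given for all 12 items, points the other way.

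**Consequence if the rule is applied as written.** In my notation, let a conversation's score be S = a·E + b·R, with E the provider's effort, R the participant's response, and a and b the weights that raters give them. The difference between arms is then

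ΔS = a·ΔE + b·ΔR.

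RQ2 asks about ΔE. With b = 0 (only provider behaviour scored), ΔS answers it. With b > 0, ΔS also carries ΔR. The article gives no value for b or ΔR, so neither the size nor the sign of b·ΔR can be worked out.

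**Do the planned safeguards remove b·ΔR?**

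- *Randomisation and adjustment for baseline differences.* These deal with differences in cognition and function that exist before the conversation. ΔR arises during the conversation, after allocation, and can itself be changed by TM. They do not remove it.
- *Inter-rater reliability.* Two raters who use the same end-points can agree closely while both score R. Agreement shows consistency and says nothing about which construct is scored.
- *Blinding.* There is none after baseline, and the mat would in any case be visible on video.

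**Reach.** The planned size is 2 arms × 50 participants × 2 conversations = 200 recordings, assuming that every conversation is recorded and rated and leaving the pilot aside. This counts the ratings to which the rule applies; it does not measure bias.

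**The case against.** The strongest reply is that a one-sentence description in an article is not the instrument. The 12 item stems, the intermediate anchors and the rater instructions are not shown, and the scale is a translation described in English. If each stem names a provider action, stem and anchor together may well score the provider. The end-points can also be read in the passive, as involved *by the provider*, which fits the construct and the section heading. This stands: the document does not establish that raters actually score the participant's state. It does not remove the conflict, because the end-points are stated in the article, not left to another document, and as stated they do not match the construct.

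A second reply also has force. Providers are trained in TM and deliver it, so using the mat is partly provider behaviour, and a score that rises for that reason is not automatically an artefact. But participant-based end-points give no means of telling that part from the participant's own activity.

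A reader might infer three stronger things that the documents do not support:

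- *That RQ2 would simply be answered by a second measure of participant involvement.* OPTION is rated by researchers from video on 12 five-point items. The IMS is six questions in which participants report their own involvement. Even on the literal reading, OPTION would not duplicate the IMS.
- *That the distortion favours TM.* This is plausible, since the article cites earlier work in which TM helped people communicate, but the direction here is assumed. Differences in MMSE between participants add noise and do not by themselves favour either arm.
- *That the cited evidence of validity does not cover these anchors.* That would need the cited source, which is not at hand.

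**Conclusion.** The concern holds in a limited form. The stated end-points for all 12 OPTION items conflict with the provider-effort construct that the article gives in three places. If raters follow those end-points, the provider-side primary outcome could be confounded with participant response. The randomised comparison of scores would remain valid as a comparison of scores, but it could not be read cleanly as an effect on provider effort.

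This rests on one assumption: that the end-points on the rating form grade the participant, as the article says, and are not turned towards the provider by the item stems or the rater instructions. The size and direction of any effect cannot be derived. The point is worth settling because it concerns one of two primary outcomes and none of the planned checks would reveal it.

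**What to change.** Reconcile the end-points with the construct. The translated rating form should carry anchors that grade the provider's behaviour on each item. If the source instrument's own anchors already do this, keep them and correct the description in the article; writing new anchors would then be unnecessary and could weaken the link to the instrument's earlier validation. Add a written instruction that raters score the provider's actions regardless of how the participant responds, and use it in rater training before the inter-rater check.

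Then establish which anchors were used for any recording already scored, including pilot recordings if they were rated with OPTION, since pilot data are to be pooled. Re-rate only those scored with participant-based anchors. The recordings are kept in secure storage, so this can be done.

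The cost is minor rater retraining and possibly some re-rating. Recruitment, allocation and sample size are unaffected.
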